### Study outcomes

The primary outcome is the proportion of unfavorable outcomes at 18 months after randomization.

Secondary outcomes include time to unfavorable treatment outcomes, time to culture conversion on liquid medium, treatment success rate at the end of treatment, proportion of recurrence at 18 months after randomization, time to recurrence after treatment completion, and adverse events of grade 3 or higher during treatment.

### Sample size calculation

The objective of this study is to determine whether the new regimen is non-inferior to the existing standard treatment. The primary outcome is an unfavorable treatment outcome at 18 months after randomization. Based on the existing study [21], a 10% unfavorable treatment outcome for the standard treatment (control group) and a 0% difference from the investigational group is assumed. To obtain a study with 80% power and a 2.5% one-sided significance level for the non-inferiority recognition limit of 6%, each group will contain 393 participants. Assuming a 15% dropout rate [22], the total number of study participants will be 926, resulting in 463 participants in each group. In the occurrence of participant withdrawal within 7 days of randomization, replacement participants may be recruited.

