**Methods:**

This study is a multicenter, open-label randomized clinical trial of non-inferiority design that compares a new regimen with the conventional regimen for drug-sensitive pulmonary TB. The investigational group will use a regimen of high-dose rifampicin (30 mg/kg/day) with isoniazid and pyrazinamide, and the treatment will be maintained for 12 weeks after the achievement of negative conversion of sputum culture. The control group will be treated for 6 months with a World Health Organization-endorsed regimen consisting of isoniazid, rifampicin (10 mg/kg/day), ethambutol, and pyrazinamide. The primary endpoint is the proportion of unfavorable outcomes at 18 months after randomization. Secondary outcomes include time to unfavorable treatment outcome, time to culture conversion on liquid medium, treatment success rate at the end of treatment, proportion of recurrence at 18 months after randomization, time to recurrence after treatment completion, and adverse events of grade 3 or higher during the treatment. We predict a 10% unfavorable outcome for the control group, and 0% difference from the investigational group. Based on 80% verification power and a 2.5% one-sided significance level for a non-inferiority margin of 6%, 393 participants per group are required. Considering the 15% dropout rate, a total of 926 participants (463 in each group) will be recruited.

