## Methods/design

### Study design

This investigator-initiated study is a prospective, multicenter, randomized, open-label, two-arm non-inferiority clinical trial. Participants with drug-sensitive pulmonary TB will be randomly assigned to one of two groups at a 1:1 ratio, and the study will be terminated 18 months after randomization.

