### Definitions

Culture of *M. tuberculosis* will be considered to be converted to negative when two or more consecutive cultures, taken at different visits, are found to be negative in liquid medium. When a participant cannot produce sputum after the first negative culture sputum, they will be considered as having achieved culture conversion. The submission date of the first confirmed negative sputum culture will be regarded as the date of culture conversion. If *M. tuberculosis* is found to be re-cultured two or more times following a negative culture conversion, this will be termed culture reversion [18]. Treatment success is defined as achieving negative culture conversion and maintaining negative cultures till the end of treatment.

The sum of treatment failure, recurrence, death during treatment (except for accidents and suicide), loss to follow-up, and withdrawal from the study will be designated as “unfavorable outcomes.” Treatment failure will be defined as participants who fail to achieve culture conversion during treatment period, or as participants using second-line anti-TB drugs for more than 4 weeks. Recurrence will be assigned to participants that indicate the presence of *M. tuberculosis* in sputum cultures for two or more times after the end of treatment.

Adverse events will be defined when undesirable medical events have occurred in participants, irrespective of a causal relationship with the treatment [19]. When adverse events result in death, life-threatening conditions, patient hospitalization or prolongation of existing hospitalization, persistent or significant disability or incapacity, or a congenital anomaly or birth defect, the events will be classified as serious adverse events. The severity of each adverse event will be assessed based on Common Terminology Criteria for Adverse Events (CTCAE) version 5.0 [20].

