## Discussion

The Hi-DoRi-3 is a phase 3 open-label, multicenter, randomized, non-inferiority clinical trial that aims to investigate the effectiveness of a high-dose rifampicin-containing regimen for the treatment of drug-sensitive TB. In this study, the effectiveness and safety of a regimen with a shortened and individualized treatment duration will be compared with the standard 6-month regimen for TB treatment. The three-drug intervention regimen will include high-dose rifampicin (30 mg/kg) with isoniazid and pyrazinamide, which will be administered until culture conversion, followed by 12-week administration of high-dose rifampicin and isoniazid.

In South Korea, the treatment success rate of TB is ~ 90%. While less than 1% of TB patients could not be cured, 5.3–25.2% of TB patients were lost to follow-up [23]. The standard 6-month regimen, comprising four drugs, has remained unchanged for almost 40 years [3]. To enhance compliance and adherence to TB treatment, simple, less toxic, and shorter regimens are needed. With the aim to shorten treatment duration in TB patients, 4-month fluoroquinolone-containing regimens were compared with the standard treatment [7–9]; however, non-inferiority of these regimens was not proven.

For the last ~ 40 years, recommendations for the maximal dose of rifampicin have been confined to 10 mg/kg or 600 mg per day [4, 17]. The peak concentration after ingestion of the currently recommended dose of rifampicin is considered to be well above the minimum inhibitory concentration of *M. tuberculosis* [13]. However, this dose is at the lower end of the dose–response curve, and the drug concentration in *M. tuberculosis* and at the site of infection has not been considered [13]. Increased rifampicin exposure led to higher bactericidal and sterilizing activity for TB according to several in vitro and in vivo studies [24–26]. In human studies, higher doses of rifampicin shortened the time to sputum culture conversion compared with the conventional rifampicin dose [12, 14, 27]. The rate of serious adverse events in patients receiving higher doses of rifampicin was comparable to that in patients receiving the conventional dose [16].

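### The 15% dropout inflation treats dropouts as leaving the analysis, but the endpoint counts them as unfavorable, so the stated 80% power does not describe the primary analysis of 926 participants

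*Protocol article*

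**What the plan says.** All of the following is in the protocol article.

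- **Rate and difference (Sample size calculation).** The planning assumption is that "a 10% unfavorable treatment outcome for the standard treatment (control group) and a 0% difference from the investigational group is assumed". The abstract repeats it: "We predict a 10% unfavorable outcome for the control group, and 0% difference from the investigational group".
- **Size (same section).** The base number comes from "80% power and a 2.5% one-sided significance level for the non-inferiority recognition limit of 6%, each group will contain 393 participants".
- **Inflation (same section).** "Assuming a 15% dropout rate [22], the total number of study participants will be 926, resulting in 463 participants in each group".
- **Endpoint (Definitions).** The composite adds treatment failure, recurrence and death during treatment (accident and suicide excepted), and the list closes with "loss to follow-up, and withdrawal from the study will be designated as" unfavorable outcomes. The primary outcome is the proportion with such an outcome at 18 months after randomization (Study outcomes).
- **Analysis set (Statistical analysis).** The mITT result has primary consideration. That set is everyone randomized who took study drug at least once. Nothing removes a participant from it for dropping out later.
- **Decision rule (same section).** Non-inferiority is concluded if the upper limit of the two-sided 95% interval for the difference, investigational minus control, is below 6%.

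**The concern.** The same event is handled in two ways. In the sample size section a dropout reduces the number analyzed. Under the endpoint definition and the primary analysis set, a dosed participant who is lost or withdraws stays in the denominator and is added to the numerator.

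The two planning rates therefore cannot describe the same trial. A composite that includes loss and withdrawal cannot total 10% if loss and withdrawal alone come to 15%.

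This matters because the variance of the difference, and hence non-inferiority power, depends on the composite rate. If that rate is above the planning value, the interval widens and a truly equal regimen can fail the 6-point margin. If 10% is already the full composite, the inflation has no role in the primary analysis and the power is higher than stated. A reader cannot tell which case applies.

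**Working it through.** **Inputs.** Control rate 10%, true difference 0, one-sided alpha 2.5%, power 80%, margin 6 points and dropout 15% (Sample size calculation); allocation 1:1 (Study design).

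**Step 1: reproduce the plan's figures.**

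n per arm = (1.960 + 0.842)² × 2 × p(1 − p) / margin² = 7.849 × 2 × 0.10 × 0.90 / 0.0036 = 392.4, rounded up to 393.

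393 / 0.85 = 462.4, rounded up to 463; 2 × 463 = 926.

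All three figures reproduce. The formula is sound; the inputs conflict.

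**Step 2: the composite rate under each reading.** Rates are taken as equal in the two arms.

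- (a) 10% is the full composite, with loss and withdrawal included: p = 0.10.
- (b, favorable end) 15% drop out and there is no other unfavorable event: p = 0.15.
- (b, unfavorable end) 15% drop out and 10% of the remainder are unfavorable: p = 0.15 + 0.85 × 0.10 = 0.235.

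Partial overlap between the 10% and the 15% falls between the two ends of (b).

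**Step 3: power with all 463 per arm analyzed.**

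SE = √(2p(1 − p)/463); power = Φ(0.06/SE − 1.96); half-width of the 95% interval = 1.96 × SE.

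| Composite p | SE | 0.06/SE − 1.96 | Power | Half-width |
|---|---|---|---|---|
| 10% | 0.01972 | 1.083 | 86.1% | 3.9 points |
| 15% | 0.02347 | 0.597 | 72.5% | 4.6 points |
| 23.5% | 0.02787 | 0.193 | 57.7% | 5.5 points |

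Simulating the 95% Wald interval rule, with 400,000 trials per scenario, gave 86.1%, 72.5% and 57.7%. At 23.5% the observed difference would have to be below about 6 − 5.5 = 0.5 points for the trial to succeed.

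**Step 4: the composite at which 463 per arm gives exactly 80%.**

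p(1 − p) = 463 × 0.0036 / (2 × 7.849) = 0.1062, so p ≈ 0.121. The protocol states no such rate.

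**Step 5: scale.** For 80% power the Step 1 formula gives 7.849 × 2 × 0.15 × 0.85 / 0.0036, or 556 per arm, at 15%, and 7.849 × 2 × 0.235 × 0.765 / 0.0036, or 784 per arm, at 23.5%. These show the size of the gap and are not a request to enlarge the trial.

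**The case against.** **The plan may be conservative.** No arithmetic is wrong, and the protocol attaches 80% to 393 per group without claiming that 463 analyzed gives 80%. If 10% is the full composite, 926 participants exceed the target. This stands for reading (a). But (a) requires loss and withdrawal to fit inside 10%, which the 15% contradicts if it refers to the same events.

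**The inflation may serve another purpose.** It could protect the per-protocol set, or cover participants who never take a dose or prove ineligible after randomization. The term dropout is not defined in the sample size section. These explanations are possible, but none is stated, and the article makes mITT primary. They reduce certainty about what was intended without removing the conflict.

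**The 58% needs an extra assumption.** It applies 10% again to those who do not drop out, although the 10% is attached to an outcome that already includes loss and withdrawal. The Discussion reports that under 1% of Korean patients could not be cured. If, as an assumption, only 1% of non-dropouts were unfavorable, the composite would be 0.15 + 0.85 × 0.01 = 15.9% and power about 70%. This stands: 58% is the low end of a range and not the expected result. A reader who infers a near coin-flip trial goes further than the documents allow.

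Three other stronger readings also lack support:

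- The Discussion says that "5.3–25.2% of TB patients were lost to follow-up". A reader might feed that range into the power formula and obtain still lower figures. It is background on Korean patients and not a planning input, and adding a further 10% on top would count loss twice.
- A reader might infer that 10% is an end-of-treatment figure lacking later loss and recurrence. The source is not available, and the article gives the 10% straight after naming the 18-month outcome.
- A reader might see a third, incompatible handling of dropout in "In the occurrence of participant withdrawal within 7 days of randomization, replacement participants may be recruited". The sentence is permissive and does not say that the withdrawn participant leaves the analysis. Recruiting a replacement is compatible with counting that participant as unfavorable.

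**Conclusion.** The point holds as an inconsistency between the planning assumptions, the endpoint and the primary analysis set. The stated 80% would describe the primary analysis only if the 15% left it, and the endpoint definition and mITT rule do not allow that for anyone who took a dose.

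For 926 participants, power is about 86% if 10% is the complete composite to month 18. It is between about 72.5% and about 58% if 15% drop out and are counted. Even the most favorable case with 15% dropout is more than 7 points below 80%.

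These figures assume equal rates in the two arms, a true difference of zero, all 463 per arm in the mITT set, and dropout meaning the loss and withdrawal named in Definitions. The direction of the error depends on which reading the sponsor intended, so the documents do not show that the trial is underpowered. The endpoint, margin, decision rule and type I error are unaffected.

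**What to change.** Make one consistent assumption in the sample size section, say what the 15% covers, and restate the power for 926:

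- (a) State that 10% is the full composite to month 18, including loss to follow-up and withdrawal; remove dropout inflation as the rationale for 463 per arm; and report about 86% power. Or
- (b) Keep 15% dropout, state the implied composite of 15% to 23.5% with the assumption behind each end, and report about 72.5% down to 58% power, with an interval half-width of up to about 5.5 points.

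In either case, track the pooled unfavorable rate, without splitting by arm, against the stated figure. A composite above about 12.1% would signal power below 80%.

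The cost is rewording plus monitoring of one pooled rate. No participants are added. The downside is that the stated power may become less favorable.

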#### Allocation concealment mechanism

It is an open-label trial. Both participants and treating physicians will be aware of allocation information.

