### Statistical analysis

The results of this trial for outcomes will be analyzed based on intention-to-treat (ITT), modified ITT (mITT), and per protocol (PP) approaches, with a primary consideration for mITT results. The ITT group will include all participants who are randomized after satisfying eligibility criteria. The mITT group will include participants who are randomized and who have received the study drugs at least once. The PP group will include participants in the mITT group who have completed the standard treatment for at least 20 of the 24 weeks for the control group or those who have completed the planned treatment for at least 10 of the 12 weeks for the investigational group. A safety analysis will be performed based on the safety group, which will include participants who have been administered with at least one dose of the investigational drugs.

For the primary outcome analysis, the frequency of occurrence of unfavorable outcomes in the control and investigational groups will be analyzed, and the incidence rate of unfavorable outcomes ($${\widehat{P}}_{T}, {\widehat{P}}_{C}$$) and the 95% confidence interval will be estimated. In this non-inferiority test, if the upper limit of the two-sided 95% confidence interval of the difference in incidence of unfavorable outcomes at 18 months between the investigational and control groups ($${\widehat{P}}_{T}-{\widehat{P}}_{C}$$) is less than 6%, it will be concluded that the investigational group is not inferior to the control group.

For the analysis of time to unfavorable outcome, time to culture conversion, and time to recurrence, the median time of each group will be estimated using the Kaplan–Meier method and will be compared with the log-rank test. Treatment success rate and recurrent rate at the end of treatment will be compared with the chi-square test or Fisher’s exact test between the two groups.

Safety will be assessed based on the occurrence of adverse events during the clinical trial period. The frequency and proportion of all adverse events, serious adverse events, and adverse events of grade 3 or higher will be summarized and compared using the chi-square test or Fisher’s exact test.

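### Participants who withdraw in the first week of this open-label trial may be replaced, and those who withdraw before the first dose leave the primary mITT analysis although withdrawal is an endpoint event

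*Protocol article*

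**What the plan says.** All of this is in the protocol article.

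- **Sample size calculation.** After deriving 926 participants, including a 15% dropout allowance, the section adds: "In the occurrence of participant withdrawal within 7 days of randomization, replacement participants may be recruited".
- **Definitions.** Along with treatment failure, recurrence and death during treatment, "loss to follow-up, and withdrawal from the study will be designated as" unfavorable outcomes. No exception is made for withdrawal soon after randomization.
- **Study outcomes.** "The primary outcome is the proportion of unfavorable outcomes at 18 months after randomization".
- **Allocation concealment mechanism.** "Both participants and treating physicians will be aware of allocation information".
- **Statistical analysis.** ITT, mITT and per-protocol analyses are planned, "with a primary consideration for mITT results". For ITT: "The ITT group will include all participants who are randomized after satisfying eligibility criteria". For mITT: "The mITT group will include participants who are randomized and who have received the study drugs at least once".

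The article does not connect the replacement sentence with the endpoint definition or with the analysis sets.

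**The concern.** The people who may be replaced have, by the trial's own definition, already had a primary-endpoint event, and they had it after the arm was known. What matters is whether that event still counts once a replacement is recruited.

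For a participant who withdraws before the first dose, the text gives a clear answer: the event does not count in the analysis that decides the trial. In an open-label trial the choice not to start can depend on the arm assigned, so leaving these participants out is not neutral in the way it might be under blinding. If such withdrawals were more frequent in the investigational arm, the primary comparison would be biased toward non-inferiority. If they were more frequent in the control arm, it would be biased the other way.

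**Working it through.** **1. The plan's own sample size.** The calculation is for "80% power and a 2.5% one-sided significance level for the non-inferiority recognition limit of 6" percentage points, with 10% unfavorable in both arms.

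n per arm = (1.960 + 0.842)² × [0.10×0.90 + 0.10×0.90] / 0.06² = 7.849 × 0.18 / 0.0036 = 392.4, rounded up to 393.

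With 15% dropout: 393 / 0.85 = 462.4, rounded up to 463 per arm, 926 in total. All three figures reproduce, and the point does not dispute them.

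**2. Where an early withdrawal ends up under the text as written**

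| Participant | ITT | mITT (primary) | Replacement allowed |
|---|---|---|---|
| Dosed, withdraws within 7 days | in, unfavorable | in, unfavorable | yes |
| Not dosed, withdraws within 7 days | in, unfavorable | not in the set | yes |

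Only the second row loses an endpoint event from the primary analysis. The loss comes from the at-least-one-dose condition; the replacement sentence then fills the gap with a new participant.

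**3. How many such withdrawals would matter.** Assumptions: 46 events among 463 in each arm of the mITT set (10% of 463 is 46.3), and k never-dosed withdrawals in the investigational arm only, which is the worst case. The primary set shows 46/463 against 46/463. ITT shows (46+k)/(463+k) against 46/463. The upper limit is d + 1.96 × √[p_T(1−p_T)/n_T + p_C(1−p_C)/n_C].

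| k | Investigational arm, ITT | Share of arm | Difference (points) | Upper limit |
|---|---|---|---|---|
| 0 | 46/463 | 0% | 0.00 | 3.85% |
| 5 | 51/468 | 1.1% | 0.96 | 4.89% |
| 10 | 56/473 | 2.1% | 1.90 | 5.89% |
| 11 | 57/474 | 2.3% | 2.09 | 6.09% |
| 14 | 60/477 | 2.9% | 2.64 | 6.68% |

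For k = 11: 57/474 = 12.03%, difference 2.09 points, standard error 2.04 points, and 2.09 + 1.96 × 2.041 = 6.09. Throughout, the primary set would still report 3.85%.

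**4. Other patterns.** With 11 never-dosed withdrawals in each arm, ITT gives 57/474 against 57/474, a difference of 0 and an upper limit of 4.14%. With 11 in the control arm only, ITT gives 46/463 against 57/474, a difference of −2.09 points and an upper limit of 1.91%. The effect therefore depends wholly on imbalance.

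**5. Effect on the error rate.** Suppose the true rates with all withdrawals counted are 16% and 10%, exactly at the margin, and a share w of the investigational arm withdraws before dosing and is replaced. The rate among the rest is q = (0.16 − w)/(1 − w). The chance of declaring non-inferiority is Φ[(0.06 − (q − 0.10))/SE − 1.96].

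| w | q | 393 per arm | 463 per arm |
|---|---|---|---|
| 0 | 16.0% | 2.5% | 2.5% |
| 1% | 15.2% | 5.5% | 5.8% |
| 2% | 14.3% | 11.1% | 12.3% |
| 3% | 13.4% | 20.5% | 23.3% |

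The values of w are assumptions. The documents give no rate of withdrawal within 7 days.

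**The case against.** **Removal of dosed failures.** A reader might infer from the word replacement that a dosed participant who leaves on, say, day 5 is taken out and exchanged for someone new. The documents do not support this. The ITT and mITT definitions make no exception for replaced participants, and the endpoint definition makes none for early withdrawal. For dosed participants, removal is a risk of loose wording and not a stated rule. This objection stands.

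**Inheriting the vacated allocation.** A reader might also infer that a replacement takes over the withdrawn participant's arm, so that the allocation is known beforehand. Nothing says so. The section on sequence generation describes remote web-based stratified block randomization, and how added participants are numbered is a detail that an article can leave to the full protocol. This also stands.

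**Direction.** Participants receive a detailed explanation before consent, so high-dose rifampicin is not news in week 1. Control participants facing the longer four-drug course might withdraw just as readily. The direction of any imbalance is therefore unknown.

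**Purpose and cause.** Replacement is not pointless: it restores the size of the primary set when never-dosed participants fall out of it. The loss itself comes from the mITT definition, so deleting the replacement sentence alone would not cure it. Both statements are correct.

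**ITT is already planned.** It does count these participants. However, the article gives mITT primary consideration and does not say that ITT must also meet the margin, so a discordant ITT result would not block the claim.

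What survives is narrow: the never-dosed participant who withdraws after learning the arm.

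**Conclusion.** The point holds in limited form. The replacement sentence is not reconciled with an endpoint that counts withdrawal as failure. For participants who withdraw before dosing, the text as written leaves the event out of the primary analysis and allows a replacement. For dosed participants, the text as written counts the event.

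The size is conditional. With 46/463 events in each arm of the primary set, about 11 one-sided never-dosed withdrawals, roughly 2.3% of the investigational arm, separate an upper limit of 3.85% from one of 6.09%. With 5 the conclusion would not change, and with equal losses in both arms the difference stays at zero. One-sided loss is the worst case, and its rate is assumed. A claim that the plan favors the new regimen, or that randomization is broken, goes beyond the documents. The change is still worth making, because it costs little and removes a route by which knowledge of the arm could affect the primary result.

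**What to change.** 1. Reword the replacement sentence in the sample size section. No randomized participant is removed from any analysis because of replacement. Withdrawal at any time counts as unfavorable in ITT, and in mITT if dosed. Any additional participant is newly randomized through the system already described under sequence generation. Alternatively, delete the sentence, since 926 already includes 15% for dropout.
2. Because deletion or rewording alone does not bring back never-dosed withdrawals, add to the statistical analysis section that non-inferiority is claimed only if both the mITT analysis and the ITT analysis, with never-dosed withdrawals counted as unfavorable, have an upper limit below 6%.
3. Report withdrawals within 7 days by arm and by whether any dose was taken.

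The cost is a few sentences. The ITT analysis is already planned, and 393, 463 and 926 do not change. The observed unfavorable rate may be slightly higher, and requiring both analyses to meet the margin loses a small amount of power. With 11 never-dosed withdrawals in each arm, for example, the ITT upper limit would be 4.14% against 3.85% in mITT.
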